## Abstract

**Clinical trial registration number:**

NCT04493957.

## Introduction

Older drivers are faced with the decision to continue or discontinue driving because of health problems, which may also include cognitive disorders. Due to population aging, the number of individuals with major cognitive disorders is increasing and should reach 65.7 million by 2030 (1). Consequently, the number of older drivers with cognitive disorders will increase over the next few years. Individuals with cognitive disorders have an increased risk of traffic accidents (2–4). The risk of individuals with major cognitive disorders being involved in a collision is up to 4.5 times higher than for older people without cognitive disorders (4, 5). Most on-road studies (4, 6–10) and simulator studies (9, 11) have also shown that, on average, the ability to drive is more affected in drivers with cognitive disorders than in drivers without cognitive disorders. Studies which take a naturalistic approach have also shown that drivers with cognitive disorders have poorer self-regulatory behavior than healthy older drivers (12). However, more than 40% of people with cognitive disorders, whose accident risk is 2–5 times higher than older adults without cognitive disorders, continue to drive (13). Almost half of the patients studied were involved in a crash in the 3 years leading up to the diagnosis of cognitive disorder (14). Driving a car may therefore become an important road-safety issue for patients with cognitive disorders.

Giving up driving is a challenging transition for older drivers, and can sometimes be difficult (15). It is a significant life-event, and can lead to major changes in lifestyle, such as a decrease in outward-looking activities, increased loneliness and social isolation. It may also result in depression (16). In France, only a certified physician (i.e., certified by the Prefect of the Department) is qualified to authorize or prohibit driving activity. Medical confidentiality regulations mean that attending physicians, geriatricians and neurologists cannot oblige patients to see their certified physician. They can only advise patients to adapt their driving or give up driving completely. Only patients themselves can impart information about their medical conditions. It is up to the patient or the family caregiver to make an appointment with their certified physician. The patient might then be required to undergo a medical check-up. Then, the certified physician will provide a medical decision about the ability to drive based on the advice of professionals. He/she also specifies the duration of this authorization or prohibition whether any restriction is recommended (e.g., vehicle adaptation, automatic gearboxes). This could lead to suspension of the driving license by the authorities (i.e., the Prefect of the Department). Unfortunately, very few patients take the step as observed in our clinical practice.

A number of intervention programs aimed at managing driving cessation in older adults have been proposed in different countries. A recent review underlined the encouraging results of these intervention programs on processing the decision (17). Only two controlled randomized studies were identified in the course of this review of the literature. One proposed an intervention based on emotional management strategies related to the issue of giving up driving. The results showed a decrease in depressive symptoms in participants who participated in the emotional management intervention, compared to those who did not (control group) (18). The other study proposed an intervention based on an interactive psychoeducational and motivational method for caregivers of patients with cognitive disorders who were still driving. Caregivers in the group which participated in the psychoeducational intervention felt better prepared to discuss giving up driving with the patient, and were less anxious about triggering anger or hurting the patient (19). However, the authors highlighted the lack of methodological consistency in the various studies. A more recent study investigated the effectiveness of a program composed of classroom workshops. These provided peripheral visual field and dynamic vision training, and a driving simulator training session to enable better prediction of driving risk. Results showed a significant increase in safe driving performance in older adults (20). An Australian study is currently being carried out in order to determine the effectiveness of an individualized self-awareness and adjustment program on improving or maintaining mobility after the transition from driving, to driving cessation (21). However, some aspects of driving cessation have never been considered in a cessation management program in older adults with major cognitive disorders. These include: the ability to implement adaptation strategies; the crucial role of the natural caregiver in the cessation process; and work on individuals' self-awareness of their difficulties, aimed at making them actors in the decision to stop driving.

A recent study suggested that older drivers with minor cognitive disorders were more likely to self-regulate their driving than drivers without cognitive disorders (22). These results are consistent with those of Raedt and Ponjaert-Kristoffersen, which showed that adaptation strategies such as avoidance of certain situations (e.g., night-time trips, peak-hour trips, on unfamiliar roads, or on roads with rough or damaged surfaces) may reduce accident risk in older adults with no major cognitive disorders (23). Charlton et al. also confirms that older adults engaged in self-regulatory driving strategies like reducing driving exposure (driving distance and/or frequency) (24). However, only 1 in 5 elderly drivers whose driving performance is declining over time correctly detect this change (25), which may hinder implementation of regulatory strategies. In addition to these factors, it also seems important to improve the use of regulatory strategies that help older drivers to anticipate and prepare for the consequences of driving cessation before it occurs. The implementation of regulatory strategies is modulated by different variables: self-awareness of health issues, the reasons that push people to continue driving (social representation, maintenance of lifestyle habits, independence), and available resources (social and family environment, infrastructure, and legislation) (26). Intervention programs based on these factors showed effectiveness in driving cessation. Studies have been carried out on older people with ophthalmological conditions- but no cognitive disorders - to find out how an educational program affects their perception of the driving difficulties they experience and of any self-regulatory strategies they may use (27). The Driving Habits Questionnaire (DHQ) was used to measure the perception of driving difficulties, and the Driver Perception and Practices Questionnaire (DDPQ) was used to evaluate drivers' attitude to road safety and self-regulation strategies. Six months after the program, results showed improvements in these measurements compared to those recorded before the intervention (e.g., drivers made fewer trips, traveled shorter distances, and avoided visually difficult situations, such as driving at night, or in foggy conditions).

The studies mentioned focus on programs which target either the patient or the caregiver. However, the interaction between patient and natural caregiver appears to be at the heart of this process (17, 28). A recent study showed that spouses play a significant role in their partners' decision to self-regulate their driving (29). The authors pointed out that intervention programs for driving cessation needed to consider the importance of interdependency in couples and its impact on their driving decisions and outcomes.

Finally, work on drivers' self-awareness and on their ability to anticipate their own difficulties also needs to be done (15). Older adults who stop driving appear to be those who are the most aware of their difficulties (26, 30).

The ACCOMPAGNE educational program presented here (ACCompanying Older drivers in the decision to Maintain or abandon the Pursuit of driving Activity in Geriatric and Neurological units) puts precisely this notion of self-awareness at the heart of the program. The objective of the proposed intervention is to help participants to become aware of their driving difficulties. The intervention was designed following the principles of therapeutic patient education. Therapeutic patient education is “a patient-centered process that addresses patient needs, resources, values, and strategies. It allows patients to improve their knowledge and skills in relation to their illness and its treatment” (31). It has positive impacts on the patient quality of life, treatment adherence and reduction in complications in different diseases such as asthma (32), diabetes (33), osteoarthritis (34) or Alzheimer's disease (35).

Natural caregivers play a major role in this intervention, whose aim is to support both the patient and the caregiver in dealing with the psycho-socio-economic consequences of driving restrictions. Indeed, programs combining caregivers and patients interventions has shown to be effective in increasing the general mental health of both caregivers and patients as well as delay the admittance in long-stay care (36). The role of the natural caregiver in the program is also to help the patient to recall the information learned during the program. The majority of patients with cognitive disorders have episodic memory impairment, which makes it difficult for them to memorize new information. This could be an obstacle to the implementation of self-regulation strategies.

### Aims and hypotheses

A randomized, controlled, single-blind trial will be conducted to assess the impact of the ACCOMPAGNE program on the implementation of self-regulatory strategies in the short and long-term in participants with mild to major cognitive disorders. We hypothesize that participants who benefit from the ACCOMPAGNE program will implement more self-regulatory strategies than those who receive conventional recommendations. The implementation of self-regulatory strategies will be assessed 2 and 6 months after the intervention. Because the objective is to investigate the effects of the ACCOMPAGNE program on the implementation of driving strategies, and the link with awareness of driving difficulties, rather than to examine participants' real driving ability, the driving simulator was chosen over on-road testing. This places drivers in a reproducible and controlled driving environment, and will be used to collect objectives as well as subjective measures of driving ability and self-awareness of this ability. For the same reasons, we will use the differences between the points of view of participants and their natural caregivers to measure the changes after the program.

The secondary objectives are to determine the effects of the ACCOMPAGNE program on (a) self-awareness of driving ability, (b) the mood and quality of life of both participant and natural caregiver, and (c) the natural caregiver's burden. We expect that the ACCOMPAGNE program will (a) increase self-awareness of driving ability (b) maintain participants' mood and quality of life despite any changes made, and (c) maintain the mood and quality of life of natural caregivers, and alleviate their burden to a greater degree than conventional care can.

## Methods/design

### Design

A national randomized, controlled, trial will be conducted. Two-hundred dyads (consisting of participants and natural caregivers) will be randomly assigned either to the ACCOMPAGNE group or to a control group. The trial will take place in four centers in France: memory clinics and geriatric units of the University Hospitals of Lyon, Reims and Tours, and the Geriatric Hospital of Mont d'Or. The effects of the ACCOMPAGNE program will be assessed 2 months and 6 months after the intervention. For 40 participants in the center in Lyon, a test will also be conducted on a driving simulator.

### Participants

Inclusion criteria: Participants must be aged between 50 and 95 years-old, must have a current driving license, and have to drive at least twice a week. Participants must have been diagnosed with a major or minor cognitive disorder in accordance with the DSM-V criteria (e.g., Alzheimer's disease, vascular disease). They must score over 18 on the Mini Mental State Examination (MMSE), and be sufficiently able to speak and write French to perform clinical evaluations and participate in workshops. The cut-off value for the MMSE was fixed at 18 because, below 18/30, patients generally present important cognitive disorders which may greatly hinder their involvement, contribution and understanding of the group intervention. Indeed, some authors used the cut-off of 18/30 to discriminate between mild and moderate or severe neurocognitive disorders (37, 38). There is no upper limit since participants are only included if they have a diagnosis of Mild or Major Neurocognitive Disorders. Thus, the presence of cognitive impairment is objectified by other means than the MMSE score.

A family member will have to accompany them and be present for at least 4 h a week. The natural caregivers must be involved in helping the participant with the activities of daily living and be able to speak and write sufficiently well to perform the clinical assessments. All participants will provide free and informed consent.

Exclusion criteria: Participants must not have any history of major psychiatric disorder, alcoholism, they should not be undergoing non-stabilized antidepressant treatment (i.e., it should not have been changed or started <6 months prior to the study), or have any sensory problems which would prevent them from participating in workshops. They must not suffer from any pathology which compromises their health in the short or medium term, and they must be able to express their consent. The natural caregivers must not have any sensory disturbances which would prevent them from participating in workshops.

To recruit the patient-caregiver dyads corresponding to the inclusion/exclusion criteria, physicians will give them information about the study when seeing them in their care pathway about cognitive complaints. Oral and (comprehensive) written information will be given to them as well as a leaflet summarizing the most important pieces of information about the aims of the study, their roles and what they could expect from it. The fact that the study cannot leads to the authorization or the prohibition of driving was emphasized. You can find the English version of the leaflet in Figure 1.

**Figure 1 F1:**
[figure not shown]
English version of the recruitment leaflet.

### Randomization

Randomization between the two groups will be stratified in the individual recruitment centers, based on participants' level of cognitive disorder (two levels: minor or major). Randomization by block permutation will be carried out in order to balance the two groups (experimental and control groups), and to allow the workshops to start in the experimental group, which requires a minimum of four dyads. The block permutations will differ in size to ensure the unpredictability of the random allocation.

### Participant timeline

There will be three assessments: a baseline assessment (Time 1), another 2 months after baseline (Time 2) and a third 6 months after baseline (Time 3), as shown in Figure 2. Participants will be randomized between two sequences (i) Baseline (Time 1)>Intervention>Time 2>Time 3 or (ii) Baseline (Time 1) >Control>Time 2>Time 3 (as shown in Figure 2). The intervention will be based on seven collective workshops, spread over three half-days (once a week for three consecutive weeks). For participants recruited by Lyon Hospital, the evaluation will also include a driving simulator test at Baseline (Time 1), Time 2 and Time 3.

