### Outcomes and assessment tools

#### Main outcome: Implementation of self-regulation strategies

The main outcome is the implementation of self-regulation strategies in driving. Self-regulation strategies will be measured by the participants' scores on the DPPQ “Current Self-Regulatory Practices” subscale (29). The 2-month and 6-month scores of the control group and the experimental group will be compared. The subscale includes eight questions about the frequency of drivers' self-regulation strategies. These strategies consist of: waiting for the rain to stop before driving; asking someone to accompany them rather than driving alone; looking for parking lots to avoid parallel parking; avoiding turning left in traffic; avoiding taking the freeway; avoiding rush-hour traffic; avoiding driving in crowded places; and avoiding driving at night. A four-point scale (0: never, 1: rarely, 2: sometimes, 3: often) reflects the frequency of each item, creating a total score ranging from 0 (never uses any of these strategies) to 24 (uses all strategies often).

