#### Secondary outcomes

-Driving changes:

The secondary objectives focus on driving changes observed by the participants themselves, and changes in the participant observed by the caregiver (see Table 2). Several indicators will be used to obtain these measurements.

**Table 2 T2:** Measurements at baseline, 2 months and 6 months after the intervention on the patient and his caregiver.

**Outcome**	**Measure**	**Filled out by the:**		
		**Patient**	**Caregiver about the patient**	**Caregiver about himself**
Implementation of self-regulation strategies in driving	DPPQ's “Current Self-Regulatory Practices” (29)	x		
Indicators of driving changes	DHQ (30)	x		
Indicators of changes perceived by the caregiver	DHQ and DPPQ scales		x	
Indicators of driving ability self-awareness	Second part of the DHQ scale, objective measures from driving simulator and subjective measures from a questionnaire administered just after each simulator task.	x		
Indicators of mood effects of driving modifications	GDS (39)	x		x
Indicators of quality of life effect of driving modifications	QoL-AD scale (40)	x		x
Indicators of caregiver burden of driving modifications	ZBI (41)			x

Indicators of driving changes in participants will be measured at 2 months and 6 months by a composite score calculated using the first part of the Driving Habits Questionnaire (DHQ) (30) and the other DPPQ sub-scales. Indicators of driving changes perceived by the natural caregiver will be measured at 2 months and 6 months by a composite score which includes scores from the DPPQ and DHQ scales, and scores calculated from observations made by the caregivers about participants' driving. Indicators of self-awareness of driving ability will be measured at 2 months and 6 months by the score obtained in the second part of the DHQ scale filled out by the participant. Those questionnaires (DPPQ and DHQ scale) are self-reported measures but since the patient and the caregiver both answer about the patient driving, we may control for most of the bias induced by such measures. Moreover, authors such as Charlton et al. showed that results with objective methods about self-regulation of driving are coherent with self reported measures (24) which supports our use of those questionnaires.

-Driving performance and self-awareness of driving ability:

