### Sample size and data analyses

The self-regulation strategy in driving will be considered beneficial if the score of “Self-Regulatory Practice” increases on average by two points (24) 2 months from inclusion. The number of subjects was computed by considering a Student *t*-test for equal variances between the two groups, with a two-sided alpha risk of 5% and a power of 80%. Based on the sample size calculation, 90 participants per group is considered sufficient to detect differences between the two assessments. Because a 10% loss of dyads is expected during the follow-up period, 100 participants per group will have to be recruited, i.e. a total of 200 participants.

Kolmogorov-Smirnov tests will be used to determine the normality of variables. For demographic, clinical, neuropsychological variables, and scores obtained from scales (e.g., the DPPQ), between-group differences will be examined using Fisher's Exact tests, independent Student *t*-tests or Wilcoxon rank-sum tests, as appropriate. The effect size in the intervention group compared to the control group will be quantified by estimating the difference in mean scores between the 2 groups (experimental vs. control) with a 95% confidence interval. A multiple linear regression model will be performed with DPPQ “Current Self-Regulatory Practices” as the dependent variable, and the level of cognitive impairment at inclusion and other characteristics that may have an effect on the outcome criterion as factors. A mixed-effect linear regression model will also be computed with DHQ, GDS-15, Qol-AD and ZBI as dependents variables, and the group (experimental vs. control) and follow-up time (inclusion, 2 and 6 months) as independent variables. The interaction between the intervention group and the follow-up time will be observed.

The concordance between the performance on the driving simulator and the perception of driving ability measured immediately after simulated driving will be estimated by the Lin concordance correlation coefficient and by the Bland & Altman method for continuous criteria, and by the Cohen Kappa coefficient for ordinal criteria. The number of participants who significantly change their estimation at 2 and 6 months compared to before the intervention will be measured from objective and subjective measures at the different points in time.

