### Procedure

Participants who are more likely to participate in the study will be identified during attendance at the memory clinics or in the geriatric departments of the four centers. The inclusion criteria will be checked during the pre-inclusion visit. During the visit to determine inclusion, a physician will take the medical history and note any comorbidities (including a diagnosis of cognitive disorder). He/she will also perform a sensory-motor examination using the Short Physical Performance Battery (balance, walking speed, chair raising), the Stop Walking when Talking (motor and verbal double task) and the Handgrip strength to detect physical frailty (Fried's criteria). Socio-demographic data and current medication will also be noted. A nurse will perform a visual examination by assessing the uni and binocular distance visual acuity (Monoyer scale) and near visual acuity (Parinaud scale). He/she will also perform a screening for age-related macular degeneration (Amsler grid), explore the visual field (with a finger) and examine the color perception. A neurocognitive examination will be performed by a neuropsychologist using the Victoria Stroop Test, the Trail Making Test (A and B), verbal fluencies (“P” and “Animals” in 2 min), the Rey Figure copy, and Digit Span and Coding from the WAIS-IV.

On the day of the inclusion visit, the neuropsychologist will administer the DPPQ, DHQ, QoL-AD, GDS-15 scales to the participant. Natural caregivers will respond by themselves to the DPPQ and DHQ scales (based on observations made about the participant's behavior), and to QoL-AD, GDS-15, ZBI. The dyads included in the control group will receive the usual medical recommendations on the same day. The dyads included in the intervention group will be invited to the three half-day workshops. Workshops will start as soon as the experimental group contains four dyads. At 2 and 6 months, the neuropsychologist will administer the DPPQ, DHQ, QoL-AD, GDS-15 scales to the participant. Caregivers will complete the DPPQ and DHQ scales, (based on observations regarding the participant's behavior), and the QoL-AD, GDS-15, ZBI on their own. A questionnaire about life events that took place between each visit will also be administered to the patient and the caregiver at 2 and 6 months. For 40 participants recruited in the Lyon center, observations on a driving simulator will be collected at inclusion, at the 2-month visit and at the 6-month visit.

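### The 2- and 6-month visits are counted from baseline in some sections and from the intervention in others, and the arm-specific wait for a workshop group makes the two origins differ.

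*Protocol article*

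**What the plan says.** The protocol article gives two origins for the visits at which the main outcome is compared.

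- **From baseline or inclusion.** Participant timeline: "a baseline assessment (Time 1), another 2 months after baseline (Time 2) and a third 6 months after baseline (Time 3"). Sample size and data analyses: the programme counts as beneficial if the self-regulation score "increases on average by two points (24) 2 months from inclusion".
- **From the intervention.** Aims and hypotheses: "The implementation of self-regulatory strategies will be assessed 2 and 6 months after the intervention". Design: "The effects of the ACCOMPAGNE program will be assessed 2 months and 6 months after the intervention". Title of Table 2, under Secondary outcomes: "Measurements at baseline, 2 months and 6 months after the intervention on the patient and his caregiver".

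The main-outcome section names no origin: "The 2-month and 6-month scores of the control group and the experimental group will be compared".

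The Procedure section starts the two arms differently. The baseline scales are given at the inclusion visit. For controls, "The dyads included in the control group will receive the usual medical recommendations on the same day". For the experimental arm, "Workshops will start as soon as the experimental group contains four dyads". The workshops then occupy three weekly half-days. The Participant timeline also gives the intended order: baseline, intervention, Time 2, Time 3.

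**The concern.** If everyone started treatment on the day of inclusion, the two wordings would differ little. Here they differ in the experimental arm only, by the wait for a group of four plus the span of the sessions. Each reading has its own cost.

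- **Origin at baseline.** Both arms are measured at the same time since randomised inclusion, so the comparison remains valid. However, a dyad that waits long enough reaches Time 2 before its workshops end, or before they begin. That contradicts the order the timeline itself sets out, and it pulls the estimated effect towards zero.
- **Origin at the intervention.** Every experimental dyad has been treated by Time 2, but its visit falls later after baseline than a control visit. The groups then differ in elapsed time as well as in treatment, in patients whose cognitive disorder may change over the interval.

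Because this affects the timing of the primary comparison, analysis cannot fully repair it once the visits have taken place.

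**Working it through.** **Inputs from the article.** Group size to start a workshop: 4 dyads (Randomization; Procedure). Three weekly sessions, so about 14 days from first to last. Two-sided alpha 5%, power 80%, Student t-test, target difference 2 points, 90 per group before 10% loss (Sample size and data analyses). Four centres (Design).

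**Plan's own figure.** The attrition step reproduces: 90 / (1 − 0.10) = 100 per group. No SD is given, so the 90 cannot be derived independently. Solving back from 90 per group and 80% power gives a standardised difference of 0.42, that is, an SD of about 2 / 0.42 = 4.76. The sample size itself is not disputed here.

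**Day arithmetic (needs no recruitment rate; 1 month = 30.44 days).** Two months is about day 61.
- Origin at baseline: time from last session to Time 2 = 61 − 14 − wait = 47 − wait. With no wait it is 47 days; with a 30-day wait, 17 days. A wait over about 47 days puts Time 2 before the last session, and over about 61 days before the first.
- Origin at the end of the intervention: experimental Time 2 = wait + 14 + 61. That is day 75 with no wait, 105 with a 30-day wait and 136 with a 61-day wait. Control Time 2 stays at about day 61 if counted from the same-day advice.

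**How often, as an illustration.** The recruitment rate is an assumption. Let experimental dyads arrive at random at rate r per centre per month, with a workshop starting at the fourth arrival. A dyad that needs k more arrivals (k = 3, 2, 1, 0 in turn) waits longer than t with probability Σ e^(−rt)(rt)^i / i!, summed over i = 0 to k − 1. Averaging over the four positions, with t = 2 − 0.5 = 1.5 months for not finished and t = 2 months for not started:

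Example, r = 2, t = 1.5 (rt = 3): 0.423, 0.199, 0.050 and 0, with mean 0.672 / 4 = 0.168.

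The diluted difference is 2 × (1 − fraction). Power is that of a two-sample t-test with 90 per arm and standardised difference 0.42 × (1 − fraction).

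| Experimental dyads per centre per month | Not finished at 2 months | Not started at 2 months | Difference if all unfinished show no effect | Power: all unfinished show no effect | Power: only not-started show no effect |
|---|---|---|---|---|---|
| 1 | 40% | 30% | 1.2 | 39% | 50% |
| 1.5 | 26% | 17% | 1.5 | 54% | 64% |
| 2 | 17% | 9% | 1.7 | 64% | 73% |
| 3 | 6% | 2% | 1.9 | 75% | 78% |

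For scale: 100 experimental dyads over four centres, shared equally, is 25 per centre. These rates therefore correspond to about 25, 17, 12.5 and 8 months of recruitment.

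**Shift under the intervention origin, same model.** The mean wait is (3 + 2 + 1 + 0) / 4 / r = 1.5 / r months. Mean experimental Time 2 is 2 + 0.5 + 1.5 / r = 4.0, 3.5, 3.25 and 3.0 months after baseline for r = 1, 1.5, 2 and 3, against 2 months in controls.

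**The case against.** The strongest reply is that the operative text already favours one origin. The only section that defines Times 1 to 3 counts from baseline, and the sample-size section agrees. The phrase about the intervention appears in an aims paragraph, a design overview and a table title, where it may be loose summary. The visit figure is not available, and the full protocol may settle the matter. This lowers the severity but does not remove the conflict: three statements, including the main hypothesis, still say something else.

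A second reply is that the authors foresaw the difficulty. The Randomization section says the blocks serve partly to let workshops start, and a pre-inclusion visit precedes inclusion, so centres could batch dyads. That is fair, and random arrivals without batching may overstate the waits. But blocks do not make dyads arrive together, and the Procedure section still has dyads wait for four with no limit stated.

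A reader might infer that the plan allows Time 2 before the workshops. It does not: the timeline states the opposite order. The accurate statement is that the start rule and a baseline-counted Time 2 do not secure that order. A reader might also infer that different centres will follow different readings; nothing in the article shows this.

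Finally, treating every unfinished dyad as showing no effect is the harsh case, since some will have attended one or two sessions. Counting only those not started is milder, and at 3 dyads per month the loss of power is small. Both cases are therefore shown.

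**Conclusion.** The concern holds as an inconsistency in the timing of the primary comparison, made material by a start rule that applies to one arm. The day arithmetic rests on the article alone: waits over about 47 or 61 days break the intended order under the baseline origin, and the intervention origin separates the arms by at least about two weeks plus the wait.

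The frequencies and power figures are illustrative. They assume random arrivals, equal centres, no batching, no effect in the dyads counted as untreated, and an SD implied by the plan's own sample size. Across 1 to 3 experimental dyads per centre per month, power ranges from about 39–50% to 75–78%. The documents do not support a single expected value.

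It is tempting to conclude that the trial's result will be biased. Under the baseline origin the comparison remains randomised and the risk is dilution. Under the intervention origin arm is mixed with elapsed time, but the article gives no rate of change on the self-regulation subscale over such an interval, so neither the size nor the direction of any bias can be stated. This is something that should be fixed, not a fatal flaw.

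**What to change.** Reconcile Aims and hypotheses, Design, Participant timeline, the Table 2 title and the sample-size section to one time origin, the same in both arms: randomisation or baseline.

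To make that origin workable, take baseline and randomise only when a centre has enough consented dyads to fill a workshop, so that the sessions end before Time 2. Record, by arm, the intervals from baseline to the last session and to each visit, so that adherence to the schedule can be reported.

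Tying control visits to the experimental dyads of the same randomisation block would be less suitable. Randomisation is stratified by cognitive level within centre and block sizes vary, so a workshop may draw on several blocks.

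The cost is protocol wording and a scheduling rule, with no extra patients or procedures. The downside is that some dyads wait longer between consent and baseline.
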